# Implementation of a Participatory Ergonomics Intervention to Reduce Musculoskeletal and Stress-Related Mental Health Risks in Australian Retail Workers: Protocol for a Randomized Controlled Trial

**DOI:** 10.2196/84864

**Published:** 2026-01-29

**Keywords:** ergonomics, implementation science, musculoskeletal diseases, occupational stress, randomized controlled trial

## Abstract

**Background:**

Worker participation has been identified as important for managing the risks of work-related musculoskeletal disorders (WMSDs) and stress-related mental health problems (MHPs). Previously identified barriers include securing long-term management support to implement risk reduction measures. Few studies evaluate how a manager or decision maker’s readiness to act influences the outcomes of a participatory ergonomics program. The Stages of Change (SoC) framework has been suggested for tailoring ergonomics interventions to managers’ receptiveness in a workplace setting.

**Objective:**

The main aim is to evaluate the implementation of the “A Participatory Hazard Identification and Risk Management” (APHIRM) toolkit in the online order fulfillment department for a sample of stores in a large retail organization, compared to usual risk management practice.

**Methods:**

This study is a cluster quasi–randomized controlled trial, comparing implementation of the APHIRM toolkit with usual safety risk management practice. As is typical for workplaces, the intervention is facilitated by the organization’s safety team. We recruited 9 control and 9 intervention stores to the study through random selection of eligible stores. Quantitative data are collected at baseline and 12-month follow-up. Qualitative data to enable a process evaluation are collected over the duration of the study. Primary outcome measures are physical and psychosocial hazard severity scores. Secondary outcomes are self-rated pain and discomfort scores and action plan implementation measures. Managers’ progression through SoC is an additional outcome measure. The primary outcome measures (physical and psychosocial hazard severity ratings) will be analyzed by variance-weighted cluster-level ANCOVA. Ethics approval was granted by the La Trobe University Human Research Ethics Committee (HEC25088).

**Results:**

Funding was provided in June 2025. Recruitment and randomization concluded in early August 2025. The intervention, including data collection, commenced in late August 2025 and is expected to conclude in September 2026. A total of 332 participants have been recruited to the study. Response rates have averaged 46% across control and intervention groups. As of January 2026, no data analyses have been conducted. Primary findings are anticipated to be published in Spring 2028.

**Conclusions:**

This study evaluates the implementation of the APHIRM toolkit survey in a multisite, large retail organization in Australia and describes the use of toolkit resources. It evaluates managers’ SoC regarding WMSD and MHP prevention and how this may influence outcomes. Findings from this study should provide additional insight on how to implement the toolkit in large organizations to reduce WMSD and stress-related MHP risk and inform future development of the content of the APHIRM toolkit. This study is anticipated to further inform tailoring of interventions to managers’ and decision-makers’ SoC.

**Trial Registration:**

OSF Registries 10.17605/OSF.IO/82R9G; https://osf.io/82r9g

**International Registered Report Identifier (IRRID):**

DERR1-10.2196/84864

## Introduction

### Background

Work-related musculoskeletal disorders (WMSDs) are one of the most frequent and costly type of compensable injuries in Australia, representing 87% of serious claims for injury or disease during 2019-2020 [1]. “Body stressing” represented 50% of all serious claims lodged in the retail trade sector from 2000 to 2021 [2]. Previous research has indicated that employers and ergonomists remain predominantly focused on controlling the biomechanical hazards associated with WMSDs [3-6]. This is despite consensus that psychosocial hazard exposures also contribute to these injuries and that exposure to multiple hazards simultaneously can have an additive or interactive effect [7-9]. Workplace psychosocial hazard exposure can also lead to a stress response in workers, which can in turn lead to mental health problems (MHPs) [10-13].

Effective WMSD and MHP prevention requires employers to address both the physical and psychosocial sources of injury risk. This requires accounting for the demands of the entire job, rather than evaluating and modifying individual tasks [4,8]. Workforce participation in all steps of the risk management process has also been identified as important to reducing WMSD risk exposure [14-16]. Multifactorial interventions, that is, multiple simultaneous actions to address sources of risk, selected from multiple levels of the hierarchy of controls, have also been supported as effective in reducing WMSD risk [17-20]. Multifactorial interventions are also supported for prevention of MHPs [21-23]. However, employer practices continue to be misaligned with the evidence regarding effective WMSD and MHP prevention [5,6,24,25].

Previous research has identified that employers’ approaches to both physical and psychosocial hazard and risk management are typically individualistic rather than system based. These studies have found that implemented changes rarely address the source of injury risk and are therefore unlikely to be effective at preventing WMSDs and MHPs [23]. A review of available WMSD risk management tools [26] identified only 3 comprehensive tools (ie, included both physical and psychosocial risk factors), that also used participative methods to facilitate all stages of the risk management process.

One of the 3 tools identified in the review [26] was “A Participatory Hazard Identification and Risk Management” (APHIRM) toolkit. This is a set of procedures that guides employers and workers through the 5 stages of the risk management cycle to address the sources of WMSD and MHP risk specific to a particular job. These procedures are implemented with guidance from a facilitator who has been trained to implement the toolkit. The procedures focus on implementing changes that address the sources of risks of WMSDs and MHPs. Studies evaluating the toolkit have supported its effectiveness in reducing the severity of exposure to physical and psychosocial hazards that can contribute to WMSDs and MHPs [27-29].

Effective WMSD and MHP risk reduction relies on management support, participation, and commitment of resources to implement identified actions [5,14,30,31]. Aligning approaches with management and workforce readiness for change has been suggested to improve the outcomes resulting from these changes [19,32-34]. The Stages of Change model (SoC) [35] is one approach to adapting the delivery of interventions in the workplace to the recipient’s readiness to change [32,36]. This model classifies individuals into one of five SoC: (1) precontemplation (unaware or unconcerned about workplace hazards), (2) contemplation (considering change but not yet ready to act), (3) preparation (intent to change in the near future), (4) action (made changes in the previous 6 months), and (5) maintenance (made changes and are working to consolidate gains and avoid relapse).

An individual’s SoC is determined by their current knowledge, attitudes, and beliefs regarding the issue in focus. The key constructs thought to influence movement through the stages are decisional balance, that is, weighing the pros and cons of changing, and habit strength, that is, the ability to sustain a target behavior over time [37,38]. A scoping review [39] identified few intervention studies performed in a workplace setting that used the SoC model. Previous studies on WMSD prevention [36,40,41] have used the SoC model to evaluate whether advice and interventions tailored to the target’s SoC are more effective at addressing WMSD hazards in the workplace. In this earlier work, both the managers’ and employees’ SoC were evaluated simultaneously, using a short questionnaire. Those in earlier SoC made a greater number of successful ergonomics changes when advice was tailored to their SoC. This suggests that such an approach has promise for improving the effectiveness of interventions aimed at making ergonomics changes in the workplace. Less attention has been paid specifically to the relationship between managers’ or decision-makers’ SoC (as a proxy for readiness to make changes) and the success of ergonomics interventions implemented in their area of control [19,31,36].

There is an opportunity to implement the APHIRM toolkit in a large retail organization and assess its impact on WMSD and MHP hazard exposure. The process evaluation conducted in this study will inform more effective toolkit implementation in organizations of similar scale and/or risk profile, accounting for managers’ SoC. Implementation science methodologies have been recommended as an approach to a process evaluation [26,42,43], to improve robustness, while maintaining a “real-world” context. This study intends to build on available evidence relating to effective WMSD and MHP risk management obtained from previous workplace-based studies, particularly those which have implemented the APHIRM toolkit. There are few published studies that describe the implementation of the APHIRM toolkit in large workplaces [44,45].

### Study Objectives

To address these gaps, the aims of this research are to evaluate the impact of APHIRM toolkit implementation on hazard exposure levels for workers in the online shopping department (online department), conduct a process evaluation of the toolkit implementation in each participating work group, and evaluate the influence of SoC on the use of APHIRM toolkit resources.

To achieve these aims, this research protocol is designed to answer the following questions: does implementation of the APHIRM toolkit reduce hazard exposure levels for workers in the online department? When implementing the APHIRM toolkit, what are the key requirements to maximize its effectiveness in reducing hazard exposures for workers in the online department? Are APHIRM toolkit resources used differently when senior leaders have different SoC?

## Methods

### Ethical Considerations

Ethics approval was granted by the La Trobe University Human Research Ethics Committee in July 2025 (approval HEC25088). Survey participants were provided with consent information before commencing the relevant surveys. These included the SoC survey for managers and the APHIRM toolkit survey for online team members at the stores included in the study. Survey response data were anonymized as part of the collection process. Participants in the risk management teams (RMTs) of the intervention group were provided with a participant informed consent survey prior to taking part in the study, as were participants taking part in interviews for the process evaluation component of the study. RMT data were deidentified at the completion of data collection. Participants completed activities related to the study during paid work time but were not provided with additional compensation for their participation.

### Registration

The trial has been registered through the Open Science Framework (osf.io/82r9g). Registration was performed after completion of recruitment and following commencement of data collection, but before data were viewed by the research team. Data collection commenced prior to finalization of trial registration to ensure that key activities in the intervention did not take place over the busy Christmas and new year period. Attempting to do so would have likely threatened survey response rates and stores’ level of participation in the intervention overall. Although ideally trial registration would have been completed prior to commencement of data collection, this outcome reflects the challenges associated with conducting research in a live workplace, including maintaining project momentum and sustaining organizational stakeholder engagement and motivation.

### Trial Design

This is a cluster quasi–randomized controlled trial. Each cluster comprises the employees and managers of an online order fulfilment department (known hereafter as the “online department”) in an individual store in a large retail organization. Clusters are described as “work groups” for the purposes of this study. The ratio of intervention work groups to control work groups is 1:1.

The APHIRM toolkit is designed so that nonexperts (ie, individuals other than ergonomists) can implement WMSD and MHP risk reduction measures in their workplaces. On this basis, a facilitator from the organization’s health and safety team is assigned to guide toolkit implementation for each work group in the intervention arm. Assignment of facilitators to work groups is based on their geographic location, relative to the location of the store. Facilitators are overseen by the organization’s ergonomics team, who monitor adherence to toolkit process and procedure. The organization’s ergonomics team are, in turn, overseen by the lead author, who is also employed by the organization in a health and safety role. The lead author is also a member of the research team. The research team monitors the conduct of the study, including compliance with ethics requirements, and guides a robust approach to the study and the subsequent evaluation. This structure is intended to achieve a study design that most closely resembles the real-world conditions in which this intervention would typically occur. A lack of blinding at the cluster level could be considered a threat to the validity of the study; however, discourse of the research-to-practice gap in musculoskeletal disorder (MSD) prevention research [15,33,46] suggests a need for published data on interventions that most resemble a real-world implementation environment. This includes the conduct of research in real workplaces, on real workers, facilitated by those with the typical skill and expertise that would be encountered in a real-world setting [18]. This design reflects a previously identified challenge for workplace safety and ergonomics practitioners, to translate methodologically “correct” research into evidence-based prevention practice in the scope of their roles [23]. The risks of assessment bias are mitigated through review of data collection, analysis, and interpretation by the other members of the research team, who are not part of the intervention.

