### Participants

Eligible clusters (“work groups”) are those stores with an online department, located within 1.5 hours’ drive of Sydney or Brisbane, Australia, which are the cities where the facilitators are based. Random sampling within eligible work groups will account for work groups with varying sales volumes and service offerings (eg, delivery to a customer’s vehicle parked outside the store, loading orders onto trucks for home delivery, and/or collection of orders by a third-party delivery driver through a service such as Uber). Managers of work groups are recruited to the study if they are the manager of the online department or store associated with the individual work group or are a manager responsible for the group of stores that the individual store or work group sits within.

Facilitators are allocated to work groups in a manner that replicates real-world conditions for toolkit implementation. These facilitators work in the organization’s health and safety team in the states where the intervention is conducted and possess a range of qualifications and experience, from a background in store management and operations through to degree-qualified health and safety professionals with varying years of experience.

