### Intervention

Clusters in the experimental group will implement the APHIRM toolkit processes and procedures with the guidance of a facilitator. The APHIRM toolkit guides work groups through the steps of the risk management cycle to address the sources of physical and psychosocial hazards that contribute to WMSDs and MHPs. Each step of toolkit implementation is delivered as a face-to-face session lasting up to 2 hours. Resources used to facilitate these sessions are freely available on the official website [47].

The first step of the process involves identifying members of the work group to act as representatives for their peers during toolkit implementation. This group is known as an RMT.

In the second step, the work group is invited to complete a survey that rates exposure to physical and psychosocial hazards, musculoskeletal pain or discomfort, and stress levels. The survey forms the hazard identification and risk assessment component of the risk management process. This survey is administered through an online portal, hosted as part of the APHIRM toolkit on its official website [47]. This enables the completion of surveys on any computer or mobile device. The survey is anonymous at the individual level, with responses aggregated to the work group (store) level.

In the third step, the results of the survey are provided to the work group, who then provide input on the work-related sources of risk relating to the identified hazards. Over the course of 10 monthly face-to-face sessions, the facilitator guides the RMT through the development and implementation of an action plan to address the sources of risk. It is anticipated that RMTs will identify a combination of actions that are specific to their individual store, as well as actions that are implemented in every store and thus require assistance from personnel above the individual store level to address.

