**Figure 1 figure1:**
[figure not shown]
Structure and timing of intervention activities. APHIRM: A Participatory Hazard Identification and Risk Management; RMT: risk management team.

Facilitators from the organization’s health and safety team are trained in the administration of the intervention by a member of the research team. This includes training on the procedures to facilitate each of the sessions that comprise the intervention, as well as data collection and ethics compliance procedures. The training is delivered using the resources provided in the APHIRM toolkit. One member of the research team and one member of the health and safety team have completed the 1-day APHIRM training workshop offered by La Trobe University on establishing and delivering the APHIRM toolkit in workplaces.

Adherence to toolkit procedures is monitored by reviewing the outputs of the work group, which are recorded in the work group’s toolkit portal on APHIRM’s official website [47]. Facilitators use an online notebook to record observations from each session, including how clusters use the resources from the APHIRM toolkit, fidelity to the toolkit procedures, and other observations that are important to the process evaluation completed as part of the study.

If the data provided at the conclusion of a session indicate that procedures may not have been correctly followed, a member of the research team will complete a follow-up session with that facilitator and the work group in question to review and prepare the work group for the next session and step in the intervention.

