#### Additional Outcome Measure

Managers’ SoC progression will be measured using the questionnaire included in Multimedia Appendix 1. The questionnaire will be administered every 3 months for the duration of the study via scheduled management meetings. Measurement is conducted for each relevant manager group: all the managers directly responsible for a work group in a store (online department and store managers), and managers with responsibility for groups of stores, known as “above-store managers.” Because of this, data for a manager with responsibility above a single store level may be considered when evaluating the implementation process for multiple stores under their direction, while SoC data for a store manager would only be considered in the process evaluation for the individual store under their management.

Movement through the SoC at each timepoint will be reported, as well as the absolute difference in stages, if any, from baseline to follow-up (ie, the total number of stages the work group’s managers moved through during the study period and whether movement was progressive or regressive through the SoC). This survey tool was selected as it has been previously validated as an instrument sensitive to detecting both workers’ and managers’ readiness to implement changes to address physical and psychosocial risk factors in the workplace [36,50,51]. SoC data will be collected and managed using REDCap (Research Electronic Data Capture; Vanderbilt University) electronic data capture tools hosted at La Trobe University [52,53]. REDCap is a secure, web-based software platform designed to support data capture for research studies.

A summary of outcome measures, analysis metrics, methods of aggregation, and measurement timepoints is included in Table 1.

**Table 1 table1:** Study measures, metrics, methods of aggregation, and frequency of measurement.

Primary or secondary	Outcome measure	Analysis metric	Method of aggregation	Participants providing data	Timepoints
Primary	Physical hazard measures	Change from baseline	Mean	Individual employees from each work group	At commencement and 12 months after commencement
Primary	Psychosocial hazard measures	Change from baseline	Mean	Individual employees from each work group	At commencement and 12 months after commencement
Secondary	Change in self-rated pain and discomfort	Change from baseline	Mean	Individual employees from each work group	At commencement and 12 months after commencement

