#### Process Evaluation

Data will be collected to enable a process evaluation of the implementation of the toolkit in intervention work groups. Observations and reflections will be recorded by facilitators after each interaction with participating clusters using an online notebook and synthesized to enable evaluation of the intervention using the “Reach, Effectiveness, Adoption, Implementation, and Maintenance” framework [54]. Observation themes will include the extent and nature of engagement of participants; reflections and feedback on participants’ comments about the intervention process and their satisfaction with the process; participants’ willingness to adopt the toolkit process and identified action plans; adherence to and deviation from toolkit processes; maintenance of implementation of toolkit processes; and actions that were implemented, to the extent possible considering the duration of the study. Observations will be recorded after each face-to-face meeting with each cluster, noting which resources from the APHIRM toolkit were used and how the resources were used. Interactions with members of the RMT or store-level managers for each cluster will be noted. Observations for above-store managers will be either linked to the clusters relevant to the observation being recorded or recorded as a separate record where there is no clear link between the interaction and specific clusters. These observations will be recorded in an online notebook by facilitators and monitored and reviewed by the research team.

This data will also be used to evaluate how different clusters use the resources provided in the APHIRM toolkit and how this relates to the cluster’s SoC.

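### Recorded toolkit use is to be related to managers' stage of change, but the facilitator who guides and records that use is assigned by location, so the two may not be separable

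*Protocol article*

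**What the plan says.** All references are to the protocol article.

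- **The question.** Study Objectives asks: "Are APHIRM toolkit resources used differently when senior leaders have different SoC".
- **How it is answered.** Process Evaluation says the collected observations will serve to "evaluate how different clusters use the resources provided in the APHIRM toolkit and how this relates to the" cluster's SoC. Neither this section nor Statistical Methods names any other factor for this comparison.
- **Who delivers.** Under Intervention, over 10 monthly sessions, "the facilitator guides the RMT through the development and implementation of an action plan".
- **Who records.** Also under Intervention, after Figure 1: "Facilitators use an online notebook to record observations from each session, including how clusters use the resources from the APHIRM toolkit".
- **Who the facilitators are.** Under Participants, they "possess a range of qualifications and experience, from a background in store management and operations through to degree-qualified health and safety professionals". Eligible stores lie near Sydney or Brisbane, "which are the cities where the facilitators are based".
- **How they are assigned.** Under Trial Design: "Assignment of facilitators to work groups is based on their geographic location, relative to the location of the store".
- **How SoC attaches to stores.** Under Additional Outcome Measure, "data for a manager with responsibility above a single store level may be considered when evaluating the implementation process for multiple stores under their direction". Randomization states that the 18 stores come from 3 store groups, 6 from each. Statistical Methods analyses store managers' and above-store managers' SoC separately.

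**The concern.** For this comparison the facilitator is part of both the exposure and the measurement. The same person shapes how a store uses the toolkit and decides what is written down about it. Facilitators were neither randomized nor balanced over stores. Stores near one another will tend to share a facilitator, and may also share above-store managers.

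Suppose one facilitator uses more of the resources, or takes fuller notes, and that facilitator's stores answer to a manager at a later stage. The table of use against SoC will then show a gradient even if readiness has no influence. The trial's answer to its third question, and any advice on tailoring the toolkit to managers' readiness, would rest on that gradient.

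**Working it through.** **1. What can be reproduced.** The article states no figure for this comparison, so there is none to reproduce. The check is a reading of the sections plus an illustration of size.

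**2. Structure.** Control stores do not implement the toolkit, so only the 9 intervention stores contribute. Facilitators are based in two cities, which implies at least 2; the number is not given. Above-store SoC may take few distinct values over the 9 stores, because all stores come from 3 groups. If SoC is the same for every store of a facilitator, SoC and facilitator are aliased and no analysis of these stores at one time point can tell them apart.

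**3. Chance baseline.** With n = 9 stores and no association,

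t = r√(n − 2) / √(1 − r²) = 0.5 × √7 / √0.75 = 1.53 on 7 df,

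which gives a two-sided probability of 0.17. So an apparent |r| above 0.5 occurs in about 17% of trials with nothing going on. Only the excess over 17% counts as harm.

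**4. Illustration.** Assumptions not in the documents:
- F = 2 to 5 facilitators, with the 9 stores spread as evenly as possible
- use = √a × facilitator effect + √(1 − a) × store noise, with a = 0.2 or 0.5
- SoC = √b × area effect + √(1 − b) × store noise, with b = 0, 0.5 or 1, and area meaning a facilitator's stores
- all effects standard normal, and no true link between SoC and use

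Share of 40,000 simulated trials per setting with |r| above 0.5, shown for a = 0.2 and a = 0.5:

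| F | b = 0 | b = 0.5 | b = 1 |
|---|---|---|---|
| 2 | 17%, 17% | 21%, 27% | 33%, 54% |
| 3 | 17%, 17% | 20%, 25% | 27%, 40% |
| 4 | 17%, 17% | 19%, 24% | 23%, 33% |
| 5 | 17%, 17% | 18%, 21% | 21%, 28% |

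Rounding SoC to five stages leaves the b = 0.5 column almost unchanged (19% to 27%). It leaves the b = 1 column at 21% to 53% among trials in which SoC differs between stores at all.

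**5. Reading.** If SoC is unrelated to area there is no excess. If half of its variation is by area, the excess is 1 to 10 percentage points. If it is wholly shared, the excess is 4 to 37 points, largest with few facilitators. With two facilitators and fully shared SoC, the comparison is simply one facilitator's stores against the other's.

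**6. What contrasts between stores sharing a facilitator can offer.** They remove the facilitator difference but leave 9 − F − 1 = 6, 5, 4 or 3 residual df for F = 2, 3, 4 or 5. When b = 1 they do not exist.

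**The case against.** The strongest reply has four parts.

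*No analysis is specified that could go wrong.* The comparison belongs to a process evaluation built on observations and reflections. No test, coefficient or threshold is given. A reader might infer that the plan has an inflated false-positive rate; the documents do not support that, because no significance test is stated. This part stands, and it is why the size above is given as an apparent pattern and not as a type I error.

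*Silence is not exclusion.* A reader might infer that facilitator is to be disregarded. The article names no covariates here but rules none out. The notes are written by facilitators, so a breakdown by facilitator remains possible, and a fuller plan may contain one. This also stands. The point rests on what is stated: assignment by location, recording by the facilitator, and a comparison by cluster SoC.

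*There are safeguards.* Facilitators are trained, and follow-up sessions are held when procedures seem not to have been followed. The ergonomics team monitors adherence and the research team reviews the notes. Outputs are held in the toolkit portal, and Ethical Considerations mentions interviews for the process evaluation. These support fidelity and offer other sources. They do not separate a facilitator's style from a manager's readiness.

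*The overlap is assumed.* Nothing says that facilitator areas coincide with store groups, and separate analysis keeps shared above-store SoC from being merged with store managers' SoC. That is correct. For store managers the overlap may be slight; for above-store managers it is plausible but not shown.

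SoC is also measured every 3 months, so change within a store can be examined with the facilitator held constant, provided the store keeps its facilitator. This helps and belongs in the remedy.

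**Conclusion.** The point holds as a caution on the third research question. As stated, the comparison of resource use with SoC can credit facilitator differences to readiness, and the described safeguards do not prevent it. Bias requires SoC to vary with facilitator or area. The article makes this plausible for above-store managers but does not show it.

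The size is illustrative only. Against about 17% by chance, a pattern of |r| above 0.5 appears in about 18% to 27% of trials if half of SoC variation is by area, and about 21% to 54% if SoC is wholly shared. The number of facilitators, both variance shares and the even spread of stores are assumptions.

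A reader might also infer that the trial's main result is compromised. It is not: the primary analysis compares randomized arms and does not relate resource use to SoC. The matter is minor in severity, but it bears on what the third question can conclude.

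**What to change.** In the Process Evaluation comparison:

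1. State how many facilitators there are and which stores each serves, and tabulate resource use and SoC by facilitator, separately for store managers and above-store managers.
2. Alongside the overall comparison, show contrasts between stores sharing a facilitator, and changes over time within a store using the 3-monthly SoC. The within-store view should compare like toolkit steps, since use is likely to change as the process advances.
3. Where SoC does not vary within a facilitator's stores, state that the two cannot be separated and do not attribute the difference to readiness.

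If any test is run on facilitator-centred values, its df should be 9 − F − 1.

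The work is a tabulation from assignments already known, and the assignment of facilitators need not change. The article reports that no data had been analysed as of January 2026, so this can still be set out in advance. The cost is in what can be claimed: few usable contrasts among 9 stores, and some comparisons declared not separable. For that reason the same-facilitator contrasts should accompany the overall comparison and not replace it.
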